#### Other analyses

All other measures will be analyzed as other analyses. The analyses will also be conducted on the participants who complete treatment, with completion being defined as finishing at least five of the eight modules of the GAF-ID. Potential selection bias associated with completion will be corrected by including unequally distributed baseline prognostic variables as independent variables in the models. We will also perform responder analysis to investigate the number of patients who recover from depressive disorder in the intervention group and the control group based on the SCID-5 interview [31].

Additionally, we also are interested in further analysing ethnic identity that might have specific impact on depression among Indonesians. Culture is one of the factors that has been reported to contribute to the experience and symptoms of depression [47]. For this purpose, the ethnic background from each participant will be reported, and particular participants with a strong ethnic identity shown by a high score on the MEIM [42] will further be profiled on their depression symptoms.

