#### Intervention: Guided Act and Feel Indonesia (GAF-ID)

The content of the GAF-ID program is based on the face-to-face BA intervention [7] and on the Dutch online BA intervention, called “Act and Feel” [28]. The GAF-ID is offered in a secure online environment and consists of a series of eight structured modules that can be completed over 8 weeks.

BA is based on the behavioral theory stating that depression is a consequence of low rates of response-contingent positive reinforcement. Therefore, BA concentrates on activating individuals to increase contact with potential reinforcers [7]. The main focus of BA is to increase potential pleasurable activities that are preplanned and mood-independent in order to enhance mood and thereby overcome depression in the long term. In BA, the participants are first taught to observe their daily mood and behaviors/activities using daily activity monitoring. They are then asked to schedule activities and increase their daily pleasurable activities. Moreover, specific attention will be given to the role of avoidance in depression and how to break the pattern from predominantly reactive behavior towards proactive behavior [7, 8, 33].

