#### Control condition: online-delivered minimal psychoeducation (PE)

In the PE group, as an active comparison condition, the minimal PE is presented as a short, online leaflet consisting of basic information about depression and basic tips on how it can be addressed, representing information that can be easily and freely accessed online outside of this program. Participants in the PE group will receive neither assistance from lay counselors nor from clinical psychologists, but provided with the same assessments as the intervention group.

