### Analysis

#### Primary analysis

The primary analysis will be conducted on an intent-to-treat basis, including all participants randomized to the study regardless of treatment adherence or attrition or the completion of outcome assessments. The PHQ-9 [30] will serve as the primary outcome measure with the main time point of effectiveness at post intervention (10 weeks from baseline). Prior to the effect analyses the baseline comparability of the two groups in terms of prognostic variable distributions will be checked. If, despite randomization important differences exist, these variables will be adjusted for in the analyses by their inclusion as covariates.

Each repeated outcome measure will be analyzed as a dependent variable using linear mixed models for fixed (treatment) and random effects models (participant) for independent variables. These models are superior for the analysis of longitudinally correlated data (within subjects) and can optimally deal with missing values, i.e. they prevent complete-case bias by incorporating all available data. In these analyses, a treatment × time interaction term will represent the effect of the intervention on the change of the outcome variable over time. Effect modification of treatment by potential moderators will be studied by including interaction terms of treatment times the moderator variable and testing their statistical significance. Potential mediation of the effect of treatment will be studied using the mediation model proposed by Preacher and Hayes [46]. All effects parameters will be supplied with a 95 % confidence interval. The two-sided significance level will be set at *p* = 0.05.

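### The supplementary completer analysis selects on a behaviour possible only in the GAF-ID arm, and baseline adjustment cannot be relied on to correct the selection as claimed

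*Protocol article*

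**What the plan says.** Under Other analyses, the protocol article says that the analyses will also be run in participants who complete treatment, with "completion being defined as finishing at least five of the eight modules of the GAF-ID". It then states: "Potential selection bias associated with completion will be corrected by including unequally distributed baseline prognostic variables as independent variables in the models".

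The two arms differ in what can be completed. GAF-ID "consists of a series of eight structured modules that can be completed over 8 weeks". In the control arm, "the minimal PE is presented as a short, online leaflet consisting of basic information about depression". Support differs too: "Participants in the PE group will receive neither assistance from lay counselors nor from clinical psychologists". In GAF-ID, the lay counselors comment on each module, prompt the next one, send reminders and telephone. According to Study design, each participant receives a login to one program or the other.

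The article does not say which PE participants enter the completer analysis. The primary analysis is separate: "The primary analysis will be conducted on an intent-to-treat basis, including all participants randomized to the study".

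**The concern.** A rule based on GAF-ID modules can be met or failed only in the GAF-ID arm. Applied literally to both arms, it leaves no controls. Applied to GAF-ID alone, it sets a subgroup chosen after randomisation against a whole randomised arm.

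Finishing five modules depends on events after randomisation, such as motivation, early response and counselor contact. The planned correction uses baseline variables only, and only those found to be unequally distributed. Imbalance may flag measured differences but says nothing about unmeasured ones. Table 1 lists no baseline measure of motivation or treatment expectancy, and no baseline variable can record early response.

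What is at stake is how the completer result is read. It addresses a fair question, the effect in people who take up the program. With the assurance attached, a difference produced by selection could be reported as the effect of the program.

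**Working it through.** **The plan's own figure.** The completer analysis has no figure of its own. The sample size supplies the scale (Power calculation: effect size 0.35, two-sided alpha 0.05, power 0.80).

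- n per arm = 2 × (1.960 + 0.842)² / 0.35² = 128.1, so 129 per arm and 258 in total.
- The t-test solution is 129.1, so 130 per arm and 260 in total. The stated 260 is reproduced.
- The planned 312 randomised gives 156 per arm if allocation is 1:1. The article does not state the ratio, so this is an assumption.

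**Inputs the article does not give (assumptions).**

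- p, the share of the GAF-ID arm finishing at least five modules: 50%, 65% or 80%.
- r, the correlation between the tendency to complete and the part of prognosis not captured by the adjusted baseline variables: −0.2, 0, 0.2 or 0.3.
- One adjusted baseline covariate explaining 25% of outcome variance.

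**Formula.** Suppose there is no treatment effect, all PE participants are kept and GAF-ID is cut to completers. With z the normal cut-off that leaves share p above it,

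bias after adjustment ≈ √(1 − 0.25) × r × φ(z)/p, in outcome SDs.

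φ(z)/p is 0.798, 0.570 and 0.350 for p = 50%, 65% and 80%. For example, at p = 50% and r = 0.2: 0.866 × 0.2 × 0.798 = 0.138 SD.

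**Simulation.** 3,000 runs per setting, 156 per arm before restriction, true effect 0, covariate adjusted. Completion also correlates 0.2 with the measured covariate.

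| p | r | Formula (SD) | Simulated bias (SD) | Share of 0.35 | Type I error |
|---|---|---|---|---|---|
| 50% | 0.2 | 0.138 | 0.136 | 39% | 19.7% |
| 65% | 0.2 | 0.099 | 0.103 | 29% | 15.4% |
| 80% | 0.2 | 0.061 | 0.060 | 17% | 9.6% |
| 50% | 0.3 | 0.207 | 0.206 | 59% | 40.7% |
| 65% | 0.3 | 0.148 | 0.150 | 43% | 27.0% |
| 80% | 0.3 | 0.091 | 0.094 | 27% | 15.2% |

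**Two contrasting cases.**

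- *Completion depends only on the measured covariate* (correlation 0.3, r = 0). The unadjusted bias is 0.120, 0.084 and 0.051 SD at p = 50%, 65% and 80%. After adjustment it is 0 to within 0.003 SD, with type I error 4.7–5.9%. Here the planned correction works.
- *Finishers have the worse unmeasured prognosis* (r = −0.2, no correlation with the covariate). The adjusted bias is −0.142, −0.101 and −0.060 SD, against GAF-ID.

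**Check on the remedy.** An instrumental-variable estimate with exposure cut at five modules assumes that assignment has no effect in those finishing none to four. Suppose p = 0.5, an effect of 0.35 in completers and half of that, 0.175, in the rest.

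- Intent-to-treat effect = 0.5 × 0.35 + 0.5 × 0.175 = 0.2625.
- Estimate = 0.2625 / 0.5 = 0.525, which is 50% above the true 0.35.

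The exposure definition therefore matters.

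**The case against.** The strongest reply is that this is one additional analysis in a condensed article. The control set for such an analysis is often left to a fuller document. The article never says that finishers are compared with all PE participants, and a purely descriptive look within GAF-ID is conceivable. That stands in part: comparison with all PE is the natural reading but not a stated one, and silence on the control set alone would not be an error. It does not cover what the article does fix, namely a one-arm completion rule and a flat statement that the selection bias is corrected.

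Three stronger readings are tempting, and the documents support none of them.

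- *The analysis will overstate the effect.* The direction depends on finishers' unmeasured prognosis, on which the article is silent. Participants who improve early might stop before module five, and counselors pursue those who do not log in, so finishing is not purely a sign of motivation.
- *The bias is 26–71% of the design effect.* A reader can get this from (1 − p) × D, where D is the prognosis gap between would-be finishers and non-finishers: 0.3 × 0.3 = 0.09 and 0.5 × 0.5 = 0.25 SD, each divided by 0.35. Those values of D are assumed, admit only one sign, and ignore the planned adjustment.
- *The trial's main conclusion is compromised.* It rests on all randomised participants regardless of adherence. The main hypothesis and the sample size do not use the completer set.

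It can also be objected that an instrumental-variable analysis at the five-module cut is not clearly less biased. That stands. Those finishing fewer modules still receive content, feedback and calls, and the fix below takes account of it.

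**Conclusion.** The point holds for a supplementary analysis. The completer comparison is not randomised, and the claim that its selection bias is corrected is unsupported. The result is open to bias, probably in favour of GAF-ID if finishers have the better unmeasured prognosis, but this is not certain.

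For 50–80% completion and a residual correlation of 0.2–0.3, with all PE participants as comparator and no true effect, the bias is about 0.06–0.21 SD, 17–59% of the 0.35 SD design effect. Type I error is then about 10–41% instead of 5%. These are illustrations on assumed inputs, not estimates for this trial. The plan should be changed here, but the primary analysis needs no change on this account.

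**What to change.** 1. Replace the assurance with a statement that selection associated with completion will be adjusted for, but that residual selection bias may remain.
2. State that all PE participants form the comparator, and label the completer result exploratory and non-randomised.
3. Estimate the effect of taking the program by an instrumental-variable analysis: randomised arm as instrument, baseline PHQ-9 and randomisation strata as covariates, PE exposure set to 0. Define exposure as any module started and, separately, as number of modules completed (a dose). The exclusion restriction is more plausible for these than for the five-module cut.
4. Keep the five-of-eight cut only as a sensitivity analysis, with its assumption of no effect below five modules written out.

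No new data are needed, since counselors already see assignments and log-in history in the program and PE participants have no GAF-ID login. The cost is a little more analysis work, wider intervals than the completer analysis, and reliance on the exclusion restriction. The dose version also relies on linearity. Even the any-module definition is not assumption-free, because counselor calls could help someone who starts no module; this should be said when the result is reported.

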### Suicidality and serious deterioration

Suicidal thoughts and tendencies will be assessed biweekly in both conditions using the PHQ-9 [30] during the study. Participants scoring at least 2 on the suicide item “Thoughts that you would be better off dead or of hurting yourself in some way” twice in a row will be contacted by a clinical psychologist via a phone call for suicide risk assessment. Moreover, serious deterioration will be detected via the biweekly measures: in case an increase in depression level measured by the PHQ-9 [30] occurs (score increase by at least 5 points with a total score of at least 15 points) and this increase is still present or even more pronounced 2 weeks later, participants will be contacted by a trained research assistant for an IDS-C interview [34] via a phone call. If the score is at least 24, then a SCID-5 interview [31] on depression and screening for other potential deteriorations will follow. A full SCID-5 interview [31] for specific section will be followed if the participants answer “yes” to either of the screening questions.

For both treatment conditions, in case of severe suicidality and serious deterioration, more intensive treatment may be required and the participant may need to be referred to a mental health professional. They will be provided with appropriate referral information when necessary. However, all participants will be asked to continue with the intervention and the assessments.

At post intervention (10 weeks from baseline), as an outcome assessment, we will conduct the SCID-5 interview [31] on depression. At this point, we will also use the SCID-5 [31] to screen for other deteriorations in all participants, followed by the full section interview if the participants answer “yes” to either of the screening questions. The same referral procedure will be applied if any serious deterioration is found.

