### Support

#### Lay counselors

We plan to recruit 20–30 persons to serve as lay counselors for this study. Our lay counselors meet the following criteria: (1) age between 20 and 40 years with no restriction on gender, (2) minimum senior high school education, (3) willing to participate fully during the trial process, (4) no professional background as a mental health specialist, and (5) willing to participate in the training for lay counselor in this study.

The focus of the lay counselors’ support is to help each participant follow the GAF-ID program by (1) explaining to the participants how GAF-ID works, (2) providing technical assistance for participants, (3) providing short feedback to each of the completed modules, and (4) reminding participants to complete each online module. The lay counselors will not provide any additional counseling.

All lay counselors receive 2 days of intensive training during which all features of the Internet-based BA are discussed and role-plays are conducted. Other technical issues addressed during the training include how to handle technical problems that may arise, how to handle participants with low motivation, and how to monitor suicidality or other serious deteriorations during the intervention. They will receive printed training modules to help them do their tasks during the trial.

To promote treatment integrity and consistency, we provided, apart from the 2 days of training, a treatment guidance protocol, a weekly structured support checklist, a participant’s short progress report template, and regular supervision by a clinical psychologist. In order to elicit and to monitor adherence, the lay counselors will fill out a weekly structured checklist on the support that they have given to each participant. To assure integrity and consistency further, the lay counselors will also be asked to write a regular short progress report on each participant. They will give both the checklist and the report to the clinical psychologists who supervised them. The clinical psychologists will then provide necessary feedback and consultations.

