#### Clinical psychologists

We plan to recruit 10–15 clinical psychologists to provide clinical supervision to the lay counselors in this trial. Each clinical psychologist will supervise three to five lay counselors. All clinical psychologists will be graduates from a formal clinical psychology program and need to be licensed as clinical psychologists in Indonesia. The clinical psychologists will receive a weekly structured support checklist and a short report of participants’ progress from the lay counselors under their supervision that they can discuss together in the regular supervision meetings.

Similar to what is provided for the lay counselors, the clinical psychologists will be provided with 2 days of intensive training on the GAF-ID program and a printed version of the training module. The training is given to make sure that the clinical psychologists are familiar with the program and can provide necessary supervision to the lay counselors.

The clinical psychologists will only have contact with participants in case of a suicidal crisis and other serious deteriorations, through phone calls. They will be equipped with the standardized procedure on when and how they should do suicide risk assessment and handle serious participant deteriorations within this trial.

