### Outcome assessments

There will be several points of assessment conducted during this study: baseline, post intervention (10 weeks from baseline), and follow-ups (3 months and 6 months from baseline). There will also be a biweekly (once every 2 weeks) assessment in between. All self-report assessments will be conducted through the Qualtrics website, with a private link delivered to the participant’s personal email at each time point. See Table 1 for the details.

**Table 1 Tab1:** Assessments

Measures	Description	Baseline (t0)	2 weeks	4 weeks	6 weeks	8 weeks	10 weeks (post intervention)	3 months (follow-up)	6 months (follow-up)
Primary measure									
PHQ-9	Depression symptoms level	+	+	+	+	+	+	+	+
Secondary measures									
SCID-5 (interview)	Current depressive disorder (major depressive disorder and persistent depressive disorder)	+					+		
IDS-SR	Depression symptoms	+					+	+	+
FQ	Fear and avoidance	+					+	+	+
MSPSS	Perceived social support	+					+	+	+
WHOQOL-BREF	Quality of life	+					+	+	+
Potential mediators and moderators									
VAS	General mood condition	+	+	+	+	+	+	+	+
PANAS	Positive and negative affects	+	+	+	+	+	+	+	+
BADS-SF	Behavioral activation	+	+	+	+	+	+	+	+
Life-events	Life events	+							
SCID-5 (interview)	• History of depressive disorders (major depressive disorder or persistent depressive disorder) • Trauma- and stressor-related disorders	+							
Childhood trauma (interview)	History of childhood trauma	+							
Additional measures									
MEIM	Multigroup ethnic identity measure	+							
Demographics	Sociodemographic characteristics	+							
Clinical information	Information related to clinical conditions	+							

*BADS*-*SF* Behavioral Activation for Depression Scale Short Form, *FQ* Fear Questionnaire, *IDS*-*SR* Inventory of Depressive Symptomatology Self-Report, *MEIM* Multigroup Ethnic Identity Measure, *MSPSS* Multidimensional Scale of Perceived Social Support, *PANAS* Positive and Negative Affect Scale, *PHQ*-*9* Patient Health Questionnaire-9, *SCID*-*5* Structured Clinical Interview for DSM-5, *VAS* Visual Analogue Scale, *WHOQOL*-*BREF* The brief version of the WHO Quality Of Life

The time frames of 2 weeks, 4 weeks, 6 weeks, 8 weeks, 10 weeks, 3 months, and 6 months are counted from baseline (applied in both groups)

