#### Primary outcome

The primary outcome is self-reported depressive symptoms based on the Patient Health Questionnaire-9 (PHQ-9) [30] at post intervention (10 weeks from baseline). However, overall during the study, it will be administered at baseline, post intervention (10 weeks from baseline), follow-ups (3 months and 6 months from baseline), as well as biweekly during the 8-week intervention period.

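### The two-in-a-row suicide-item trigger does not fit the follow-up schedule: under the stated rule a positive first seen at month 3 waits 12–13 weeks for a psychologist's call, and one first seen at month 6 cannot trigger it

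*Protocol article*

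**What the plan says.** The section *Suicidality and serious deterioration* sets the monitoring frequency: "Suicidal thoughts and tendencies will be assessed biweekly in both conditions using the PHQ-9 [30] during the study". It then sets the trigger: participants with a score of 2 or more on the PHQ-9 suicide item "twice in a row will be contacted by a clinical psychologist via a phone call for suicide risk assessment". No other score-based trigger for that call is stated, and no separate rule is given for the follow-up visits.

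The PHQ-9 schedule is fixed elsewhere. *Primary outcome* lists baseline, week 10 and the two follow-ups, "as well as biweekly during the 8-week intervention period". Table 1 under *Outcome assessments* shows the same pattern, and its footnote says "The time frames of 2 weeks, 4 weeks, 6 weeks, 8 weeks, 10 weeks, 3 months, and 6 months are counted from baseline". The mode of collection is also stated: "All self-report assessments will be conducted through the Qualtrics website", with the link sent by email.

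Two other statements bear on the point. On the supervising psychologists, the article says "They will be equipped with the standardized procedure on when and how they should do suicide risk assessment"; that procedure is not reproduced. Lay counselors, who serve the GAF-ID arm only, are trained in "how to monitor suicidality or other serious deteriorations during the intervention".

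**The concern.** Requiring two consecutive positives is a reasonable way to limit false alarms when assessments are two weeks apart, because confirmation comes quickly. The same rule behaves very differently when the next assessment is three months away or does not exist. The article describes the monitoring as biweekly for the whole study, but its own schedule makes it biweekly only to week 10.

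What is at stake is participant safety. At months 3 and 6 the trial would hold a new suicide-item score of 2 or more from someone enrolled with a depressive disorder. The rule printed in the article would not by itself prompt anyone to telephone. Because the answers arrive through an online form, completing the questionnaire involves no conversation in which the answer would be noticed.

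**Working it through.** No sample-size or test calculation is involved. The check compares the trigger with the schedule.

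**Inputs.** PHQ-9 at weeks 0, 2, 4, 6, 8 and 10, month 3 and month 6, all counted from baseline (Table 1). Trigger: item score of at least 2 at two consecutive assessments (*Suicidality and serious deterioration*). The article does not convert months to weeks, so I read months 3 and 6 as either weeks 12 and 24 or weeks 13 and 26.

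**Step 1: does the stated two-week interval hold?** There are seven intervals between the eight assessments. The five from week 0 to week 10 are 2 weeks each, as stated. Week 10 to month 3 is 12 − 10 = 2 or 13 − 10 = 3 weeks. Month 3 to month 6 is 24 − 12 = 12 or 26 − 13 = 13 weeks. So biweekly assessment holds to week 10 but not for the whole study.

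**Step 2: shortest time from a first positive to a call under the rule.** This equals the gap to the next PHQ-9.

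| First positive seen at | Next PHQ-9 | Shortest delay |
|---|---|---|
| Weeks 2, 4, 6, 8 | 2 weeks later | 2 weeks |
| Week 10 | month 3 | 2–3 weeks (SCID-5 also done at week 10) |
| Month 3 | month 6 | 12–13 weeks, and only if positive again |
| Month 6 | none | rule cannot be met |

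Relative to the biweekly phase, the month-3 delay is 12/2 = 6.0 to 13/2 = 6.5 times as long. The affected assessments are months 3 and 6, that is, 2 of 7 after baseline. Only first positives are affected: week 10 paired with month 3, and month 3 paired with month 6, can still satisfy the rule.

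**Step 3: does another stated step cover months 3 and 6?**
- *SCID-5.* Table 1 schedules it at baseline and week 10 only, and the screen of all participants for other deteriorations is placed at week 10. *Main study hypotheses* expects SCID-5 results at the follow-ups too, so the article is not consistent on whether an interview takes place then.
- *Lay counselors.* Their monitoring is described for the intervention period, and their last scheduled call is at week 8.
- *Deterioration rule.* It is tied to the biweekly measures and a recheck two weeks later, so it does not reach these visits.
- *Psychologists' procedure.* It is said to govern when and how risk is assessed, but its content is not shown.

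None of the steps whose content is printed fills the gap with certainty; the procedure might.

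**Step 4: effect of the change.** With a single-score trigger at months 3 and 6, the wait after a month-3 positive falls from 12–13 weeks to none, and a month-6 positive becomes actionable. With a repeat within about 2 weeks, both are resolved in about 2 weeks.

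**The case against.** The strongest reply is that this is a condensed article and the psychologists' procedure is exactly where one would expect visit-specific triggers. This stands in part: the article does not show that no call would occur, only that the printed rule does not produce one. It does not dispose of the point, because the rule and the schedule are both printed and do not fit together.

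A second reply is that the two-score rule was meant only for the biweekly phase. That is a natural reading of the trigger, but the text says the monitoring runs during the study. If the narrower meaning was intended, the article states no suicide-item rule for follow-up, and the same amendment is needed.

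Third, psychologists may contact participants in a suicidal crisis without a two-score condition, and nothing forbids a prompt discretionary call. This is correct. It leaves the response to a recorded score to discretion.

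Fourth, acute suicidality is an exclusion and everyone has the week-10 SCID-5. Both reduce risk up to week 10, but neither addresses a positive that first appears later.

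A reader might also infer that control participants have no safety provision, since the control-condition section says "Participants in the PE group will receive neither assistance from lay counselors nor from clinical psychologists". The documents do not support that. The sentence describes what the control condition delivers. The section on suicidality applies the monitoring, calls and referral to both arms.

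**Conclusion.** The point holds as a mismatch between a stated safety rule and the printed schedule. Under that rule, a suicide-item score of at least 2 first seen at month 3 cannot trigger a call for 12–13 weeks, and then only if repeated; one first seen at month 6 cannot trigger a call. This concerns first positives at 2 of 7 post-baseline assessments, equally in both arms.

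It would go too far to conclude that such participants would not be contacted, or that follow-up has no safety procedure. The unseen procedure may cover these visits, and the printed rule sets a minimum without barring other contact. The number of participants affected is unknown, because the article gives no rate of new positives. The delays rest only on Table 1 and on reading a month as 4 to 4⅓ weeks. The primary endpoint and its analysis are unaffected. This is an inexpensive improvement worth making, not a flaw in the trial's inference.

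**What to change.** In *Suicidality and serious deterioration*, limit the biweekly two-score rule to baseline through week 10. Then add that at months 3 and 6 a single suicide-item score of at least 2 triggers the existing psychologist call in both arms. If the clinical lead prefers to keep the persistence requirement, add instead a repeat of the item within about 2 weeks, with the call if it is again at least 2. The choice between the two is clinical. If the psychologists' procedure already does either, citing it at this place is enough.

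**Cost.** A short amendment with ethics notification; no new visit, instrument or staff for the single-score option, and a brief repeat item for the other. For the single-score option, the planned 20% attrition leaves 312 × 0.80 = 249.6, about 250 assessed, so each 1% of new positives is about 2.5 calls per visit, or 5 over both. At an assumed 2–10% per visit (the article gives no figure), that is about 10–50 calls in all. With the planned 10–15 psychologists, the load is between 10/15 = 0.7 and 50/10 = 5 calls each. Some would be false alarms, and some month-3 calls would only bring forward calls that the present rule would make at month 6.
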